### Primary outcome measure

#### Primary outcome

Severity of asthma: before, during and after the I-MUR service provision assessed using the ACT score.

#### Secondary outcomes

Number of active ingredients used by patients during and after the I-MUR service provision, as reported by patients.Number of PCIs identified during the I-MUR service provision, classified using the method of Krska et al.Patients’ adherence to asthma medication during and after the I-MUR service provision, measured using questions embedded within the I-MUR instrument.Cost estimated on the severity of asthma, before, during and after the I-MUR service provision.

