**Methods/Design:**

This is a cluster randomised controlled trial of the I-MUR service. Data will be collected over time before, during and after pharmacists’ intervention. Fifteen Italian regions will be involved and it is aimed to recruit 360 community pharmacists and 1800 patients. Each pharmacist will receive training in medicines use review, recruit five patients, administer the Asthma Control Test and provide the I-MUR service. Pharmacists will be allocated to different groups, one group will be trained in and provide the I-MUR service immediately after completion of the baseline ACT score, the other group will receive training in the I-MUR and provide this service three months later. Group allocation will be random, after stratification by region of Italy. The I-MUR service will involve gathering data following each patient consultation including demographic details, patients regular medications, including those used for asthma, their attitude towards their medications and self-reported adherence to treatments. In addition, pharmacists will identify and record pharmaceutical care issues and any advice given to patients during the I-MUR, or recommendations given to doctors. Pharmacists will upload trial data onto a web platform for analysis. The primary outcome measure is the severity of asthma before, during and after the I-MUR assessed using the Asthma Control Test score. Secondary measures: number of all active ingredients used by patients during and after the I-MUR, number of pharmaceutical care issues identified during the I-MUR, patients’ self-reported adherence to asthma medication during and after the I-MUR, healthcare costs based on the severity of asthma, before, during and after the I-MUR service provision.

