In Italy no other work has been conducted on asthma involving community pharmacists, therefore this current study is needed to determine whether the I-MUR can contribute to improve asthma outcomes and to demonstrate whether the service provides clinical and cost benefits, as these were not included in pilot work. The study will provide evidence about the practicability and costs of provision and the effectiveness of the I-MUR in asthmatic patients.

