## Methods/Design

### What are the principal research questions to be addressed?

Is the I-MUR service provided by community pharmacists in Italy effective in:I.Reducing the severity of asthma as assessed by the Asthma Control Test (ACT) score?II.Optimising the number of medicines (active ingredients) used by patients?III.Identifying and resolving pharmaceutical care issues?IV.Improving patients’ adherence to asthma medications?V.Reducing costs (direct and indirect) related to the reduction of the severity of asthma?

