### I-MUR

This will take place in the pharmacy private consultation area. The estimated time for the consultation will be 26 minutes based on phase one experience.

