### Data analysis

In studies where the important baseline factors seem well balanced, it is likely that any differences in outcome between intervention and control groups are a real effect of treatment, which is one component of the internal validity. Patients’ location, age, gender and ACT score will be collected and compared at baseline. This baseline ACT score will provide information regarding the level/severity of asthma prior to intervention delivery.

Quantitative data gathered through the web platform (Qualtrics^©^) will be exported and analysed using SPSS version 22. Patient location, age, gender and ACT score will be compared at baseline.

Asthma severity assessed by ACT score will be analysed over time within individual patients to obtain a percentage change score. Scores will be compared between groups at all times points. The number of active ingredients in use and reported adherence to treatment will be compared at three time points after provision of the I-MUR. The number of PCIs identified and advice given by pharmacists will be captured for both groups separately and combined. Any change in the severity of asthma and the accompanying percentage variation in cost (based on peer reviewed published data) will also be assessed. It will be possible to compare data before and after the I-MUR intervention for group A and B, separately and combined. In addition findings will be analysed by region.

A significance level (alpha) of 0.05 will be used in all analyses. Between-group differences at baseline will be compared using independent Student’s t-test for continuous parameters and Pearson’s χ^2^ will be used for categorical parameters. Outcomes for continuous parameters will be evaluated using repeated measures multivariate ANOVA.

The analysis will be conducted in two steps. Step one will represent an interim analysis after the first six months, after completion of T6, by which time all patients will have been followed up for three months after the intervention. Step two will represent the final analysis, which will be conducted at the end of the study after T9.

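### The cost outcome is published cost mapped onto ACT severity with no delivery cost, so it cannot show the net cost benefit or costs of provision that the Background says the study will address

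*Protocol article*

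**What the plan says.** All references are to the protocol article.

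- **Outcome.** Secondary outcomes lists "Cost estimated on the severity of asthma, before, during and after the I-MUR service provision". The abstract matches it: "healthcare costs based on the severity of asthma, before, during and after the I-MUR service provision".
- **Method.** Data analysis states: "Any change in the severity of asthma and the accompanying percentage variation in cost (based on peer reviewed published data) will also be assessed".
- **Severity measure.** The primary outcome is "Severity of asthma: before, during and after the I-MUR service provision assessed using the ACT score", so the same instrument drives both outcomes.
- **Research question V.** This asks about "Reducing costs (direct and indirect) related to the reduction of the severity of asthma".
- **Wider aim.** The last paragraph of the Background section on the I-MUR says the study is needed "to demonstrate whether the service provides clinical and cost benefits, as these were not included in pilot work", and adds: "The study will provide evidence about the practicability and costs of provision and the effectiveness of the I-MUR in asthmatic patients".
- **Delivery inputs.** The I-MUR section under Methods says: "The estimated time for the consultation will be 26 minutes based on phase one experience". Pharmacist training describes a half-day session. Neither is given a cost.
- **Data items.** Planned intervention and Data collection list medicines, adherence, care issues and advice. The repeated items are ACT, adherence and the number of active ingredients. No visits, admissions, lost work or delivery costs are listed, and the medicine counts are not costed.

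**The concern.** The cost result is calculated from the ACT result, so it cannot contradict it. It also leaves out the side of the account on which the service costs money: pharmacist time, training, and any extra consultations or medicines that follow referral or better adherence. The article itself treats some of these as relevant. Its account of the Isle of Wight project sets the cost of training against the savings.

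Followed as written, the plan gives a gross modelled saving. A reader who takes that as the answer to the Background's question about cost benefits could conclude that the service pays for itself when the omitted term decides the matter. The Conclusion says the results are to inform policy, and the Background says the government is considering introducing the service.

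**Working it through.** The plan states no figure for the cost outcome, so there is none to reproduce. The check has three steps.

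**1. Is cost a function of ACT?** Severity is ACT. Cost is assigned from severity using published values, and no other cost input is listed. The published values quoted in the Background are lower for better control, so any mapping that follows them gives a lower or equal cost when a patient's ACT rises. If costs are assigned by the control cut-off (19 or less against 20 or more, Proposed sample size), the sign of the group cost change is set by the change in the proportion controlled.

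**2. What is a shift worth?** Inputs, from the Background section on the problem to be addressed:
- well controlled: EUR 379 a year (95% CI 216 to 541)
- poorly controlled: EUR 1,341 a year (95% CI 978 to 1,706)

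Using these is an assumption, because Data analysis names no source. The two means are treated as independent with normal intervals.

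- Difference: 1,341 − 379 = EUR 962.
- SE, well controlled: (541 − 216)/3.92 = 82.9. SE, poorly controlled: (1,706 − 978)/3.92 = 185.7.
- SE of difference: √(82.9² + 185.7²) = 203.4.
- Approximate 95% CI: 962 ± 1.96 × 203.4 = 563 to 1,361, or about ±41%.
- Each 1-point shift to controlled: 0.01 × 962 = EUR 9.62 per patient-year (5.63 to 13.61). Over three months: 9.62/4 = EUR 2.405.

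**3. What does the omitted term do?** Quantities in the article: 1,800 × 26/60 = 780 consultation hours, and half a day of training per pharmacist, which is 0.5/5 = 0.1 day per trial patient. The article gives no price for either. The range of EUR 20 to 60 per patient is assumed.

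Break-even shift = delivery cost / value of a 1-point shift:

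| Assumed delivery cost | Benefit lasts 12 months | Only 3 months counted |
|---|---|---|
| EUR 20 | 20/9.62 = 2.1 points | 20/2.405 = 8.3 points |
| EUR 60 | 60/9.62 = 6.2 points | 60/2.405 = 24.9 points |

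Share of the gross saving used up by EUR 20 to 60:

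| Assumed shift | Gross saving, 12 months | Share | Gross saving, 3 months | Share |
|---|---|---|---|---|
| 10 points | EUR 96.20 | 21% to 62% | EUR 24.05 | 83% to 250% |
| 20 points | EUR 192.40 | 10% to 31% | EUR 48.10 | 42% to 125% |

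The 20-point row reads the plan's 20% planning difference as a shift in the proportion controlled.

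Three months is the length of the randomised contrast, because group B receives the I-MUR at T3. Twelve months is an extrapolation beyond it. The net result depends on both the horizon and the delivery cost.

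**The case against.** The strongest defence is that the outcome does what research question V asks. That question is confined to costs tied to a reduction in severity, the outcome is openly labelled as estimated from severity, and nothing presents it as independent of ACT or net of delivery cost. This stands. The mismatch is with the wider Background wording, not with question V. The article is also a condensed account, and the full protocol may cost delivery. However, the outcome as defined here does not include it, while the same article says the study will give evidence on it.

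A reader might draw three stronger conclusions, none of which the article supports:

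- **That every ACT gain must appear as a saving.** The mapping is not specified. Under costing by category, a gain within a category changes cost by zero.
- **That uncertainty in the published costs is ignored.** The article does not say how it will be handled, and that may properly sit in the analysis plan. The quoted intervals show only that it matters.
- **That a favourable cost conclusion is promised.** The text asks whether there are cost benefits.

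It is also fair to object that setting a one-off delivery cost against one quarter's benefit is a choice of horizon. It should not be the only comparison shown.

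**Conclusion.** The point holds as an internal mismatch. The cost outcome is a fixed mapping from ACT severity to published cost with no delivery term. It answers question V but cannot show a net cost benefit or the costs of provision. Neither the primary outcome nor the design is affected.

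The size is conditional. It rests on the Background costs being the source, costing by control category, an assumed delivery cost, and a stated duration of benefit. Under those assumptions the omitted term ranges from a modest deduction to more than the whole gross saving. The documents do not show that the service would cost more than it saves, only that the planned outcome could not tell.

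**What to change.** Either of two changes resolves it.

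1. **Add delivery cost.** Define the outcome as modelled severity-related cost plus I-MUR delivery cost: consultation time (26 minutes, or as recorded) and half-day training spread over the patients served. Compare net modelled cost between groups at T3, with annual unit costs scaled to the period observed. Show a longer horizon as a stated assumption.
2. **Narrow the claim.** Limit the conclusion to modelled gross severity-related cost, and remove the Background wording on cost benefits and costs of provision.

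In either case, report the result as modelled and not as evidence separate from ACT. As a recommendation, carry the confidence intervals of the published costs through to the result, for example by resampling.

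The first option needs a revised outcome definition, a source for pharmacist time and training prices, and some extra analysis. Its downside is a less favourable and wider cost figure. The second needs only a change of wording.

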## Discussion

This study has been developed because of the need for a new way of working for pharmacists and pharmacy in Italy. If the results are positive, the study has the potential to open up a new professional perspective for Italian community pharmacists, providing this is accepted by all stakeholders: Italian medicine control agency (AIFA = Agenzia Italiana del Farmaco), Italian Ministry of Health, Italian general practitioners and hospital doctors.

It is also important internationally, as it is one of the largest studies ever conducted in community pharmacy and the first and largest study ever conducted in Italy, involving 75% of Italian regions.

## Conclusion

This is the first trial of any community pharmacy-based pharmaceutical care intervention to be carried out in Italy. The results of this study will inform future policy and practice in Italian community pharmacy.

### Strengths and limitations

This is the first study conducted in Italy aiming to assess pharmacists’ contribution to reducing the severity of asthma; it is one of the largest studies conducted in one single country and it introduces a new systematic and quantitative research instrument: I-MUR.

The study includes only adults, does not require spirometric testing and will run for nine months. We do anticipate, given the size of the study, that problems may arise, for example, with pharmacist and patient recruitment, resulting in the study being underpowered. However we have taken account of this in our power calculation, by evaluating four possible options based on actual results from phase one. There is also the possibility of a higher drop-out rate than anticipated and, while the study will enable us to assess whether ACT score is a suitable primary outcome measure, this may prove not to be the case.

### Ethical consideration

Ethical approval was obtained from the Faculty of Science Ethics Advisory Group for Human Participants on 18th February 2014 (reference number 0281314) from the University of Kent (UK), and in Italy on June 3rd 2014 by the Ethics Committee of Spedali Civili di Brescia (Lombardia region) with reference number NP 1710, which is acting as the reference committee for all Italian participating regions.

## Abbreviations

ACT: Asthma Control Test
AIFA: Agenzia Italiana del Farmaco (the equivalent of MHRA in England)
DALYs: Disability-adjusted life years
FOFI: Federazione Ordini Farmacisti Italiani/Italian Pharmacists Federation
GINA: Global Initiative for Asthma
GP: General Practitioners
ICC: Intra cluster correlation
MRC: Medicine Research Council
MUR: Medicines use review
NICE: National Institute for Health and Care Excellence
PCI: Pharmaceutical care issue
PI: Principal Investigator
RCT: Randomised controlled trial
SPSS: Statistical package for the social science/statistical product and service solutions
T0: Time zero
T3: Time at three months
T6: Time at six months
T9: Time at nine months
